## Abstract

**Background:**

Primary total knee replacement is a common operation that is performed to provide pain relief and restore functional ability. Inpatient physiotherapy is routinely provided after surgery to enhance recovery prior to hospital discharge. However, international variation exists in the provision of outpatient physiotherapy after hospital discharge. While evidence indicates that outpatient physiotherapy can improve short-term function, the longer term benefits are unknown. The aim of this randomised controlled trial is to evaluate the long-term clinical effectiveness and cost-effectiveness of a 6-week group-based outpatient physiotherapy intervention following knee replacement.

**Methods/design:**

Two hundred and fifty-six patients waiting for knee replacement because of osteoarthritis will be recruited from two orthopaedic centres. Participants randomised to the usual-care group (*n* = 128) will be given a booklet about exercise and referred for physiotherapy if deemed appropriate by the clinical care team. The intervention group (*n* = 128) will receive the same usual care and additionally be invited to attend a group-based outpatient physiotherapy class starting 6 weeks after surgery. The 1-hour class will be run on a weekly basis over 6 weeks and will involve task-orientated and individualised exercises.

The primary outcome will be the Lower Extremity Functional Scale at 12 months post-operative. Secondary outcomes include: quality of life, knee pain and function, depression, anxiety and satisfaction. Data collection will be by questionnaire prior to surgery and 3, 6 and 12 months after surgery and will include a resource-use questionnaire to enable a trial-based economic evaluation. Trial participation and satisfaction with the classes will be evaluated through structured telephone interviews. The primary statistical and economic analyses will be conducted on an intention-to-treat basis with and without imputation of missing data. The primary economic result will estimate the incremental cost per quality-adjusted life year gained from this intervention from a National Health Services (NHS) and personal social services perspective.

**Discussion:**

This research aims to benefit patients and the NHS by providing evidence on the long-term effectiveness and cost-effectiveness of outpatient physiotherapy after knee replacement. If the intervention is found to be effective and cost-effective, implementation into clinical practice could lead to improvement in patients’ outcomes and improved health care resource efficiency.

**Trial registration:**

ISRCTN32087234, registered on 11 February 2015.

## Background

Knee osteoarthritis (OA) is the leading cause of pain and disability in older people [1]. If pharmacological and conservative treatments do not relieve symptoms, primary total knee replacement (TKR) is commonly performed. In 2013, over 70,000 TKR operations were performed in the National Health Service (NHS), with 96 % of procedures subsequent to OA [2]. Although the operation is effective for many patients, a considerable proportion of patients experience long-term pain and functional limitations after surgery [3, 4]. An estimated 20 % of patients report long-term pain after TKR [3] and 52 % of patients report functional limitations, compared to 22 % of age- and gender-matched people without TKR and no previous history of knee disorders [4]. Evidence also suggests that many patients do not return to more demanding activities after TKR, such as gardening [4, 5], kneeling [6], sports [7] and valued leisure activities [8].

Prior to consideration of surgical intervention, exercise can be beneficial in improving knee function for patients with OA [9], and exercise is recommended as a conservative strategy to manage the symptoms of OA [10]. Once listed for TKR, a pre-operative exercise programme may be offered to patients with the aim of maximising post-operative recovery and function. However, systematic reviews have found that post-operative function is not improved by pre-operative exercise [11–13]. This indicates the need to evaluate rehabilitation interventions delivered after surgery. Physiotherapy in the immediate post-operative period is a standard component of post-surgical care. However, rehabilitation at this early recovery stage is predominately targeted at joint mobilisation and the achievement of short-term functional goals relating to hospital discharge. Therefore, the optimal time to deliver interventions targeted at improving long-term function after TKR may be in an outpatient setting after hospital discharge. However, research has identified international variation in the provision of these services [14–18], and no UK guidelines for outpatient physiotherapy after TKR currently exist.

In a systematic review and meta-analysis of six randomised trials published prior to 2007, outpatient physiotherapy was found to improve physical function in the first 3–4 months after TKR [19]. An recent updated systematic review and meta-analysis including 17 randomised trials also found evidence of short-term functional benefits [20]. However, both reviews found there was insufficient evidence to determine whether benefits were retained in the longer term. Physiotherapy should address patient expectations [21], and the key expectations of patients undergoing TKR surgery relate to long-term functional and pain outcomes [22, 23]. Therefore, there is a need to evaluate the individual and societal burden of long-term pain and functional limitations after TKR. Functional outcomes after TKR plateau at around 12 months post-operative [24] and consequently trials with at least 12 months’ follow-up are needed to establish the long-term effectiveness of post-discharge physiotherapy after TKR.

The aims of this randomised controlled trial (RCT) are to determine the clinical effectiveness and cost-effectiveness of a novel group-based outpatient physiotherapy intervention consisting of task-oriented and individualised exercises for improving long-term function for NHS patients receiving primary TKR because of OA.

## Methods/design

The ARENA study (Activity-orientated REhabilitation following kNee Arthroplasty) is a multi-centre, pragmatic, superiority RCT to evaluate the long-term effectiveness and cost-effectiveness of outpatient group-based physiotherapy after TKR in addition to usual care. The trial has been approved by the National Research Ethics Committee South West – Central Bristol (reference 14/SW/1144) and is registered on the ISRCTN registry (ISRCTN32087234). The trial is informed by a feasibility study of the RCT with 46 patients and a 6-month post-operative follow-up [25]. In this study, the intervention was developed and the feasibility of delivering the intervention to patients with TKR in the context of a RCT was evaluated. The trial was developed in collaboration with the Patient Experience Partnership in Research (PEP-R) group [26], a dedicated, specialised patient-involvement group comprising 16 patients with musculoskeletal conditions, many of whom have had joint replacement.

### Study duration

Recruitment of the trial began in March 2015 and 12-month follow-up for all participants is anticipated to be complete by December 2017.

### Participant recruitment

NHS patients will be screened and recruited from pre-operative assessment clinics at two elective orthopaedic centres in Bristol: Southmead Hospital and Emersons Green Independent Treatment Centre. Inclusion criteria include NHS patients aged 18 years or older who are listed for primary TKR due to OA. Exclusion criteria include (1) patients listed for TKR for reasons other than OA, (2) patients listed for revision TKR, (3) inability to participate in exercise for medical reasons such as unstable cardiovascular or severe neurological conditions, (4) unable or unwilling to attend physiotherapy classes after surgery, (5) unable or unwilling to provide informed consent, (6) inability to understand English because not all the questionnaires have been translated and validated into other languages, and (7) post-operative complication(s) or interventions within the first 2 weeks of surgery which would preclude participation in the physiotherapy classes; for example, prosthetic joint infection or manipulation under anaesthetic. Participation in pre-operative physiotherapy was not a selection criterion for this trial. In order to explore whether the patients who are enrolled in the trial are representative of those undergoing TKR, anonymised data about age and gender will be recorded for all eligible patients. After patients who wish to participate in the trial have provided written, informed consent, they will be asked to complete a pre-operative questionnaire.

### Randomisation

Participants will be randomised with a 1:1 treatment allocation to the intervention group or usual care group 2 weeks after TKR. Prior to randomisation, eligibility criteria will be reassessed through contact with participants and review of operation notes. Randomisation with allocation concealment will be conducted by means of a computer-generated code, administered centrally and communicated via the Internet (through the Bristol Clinical Trials and Evaluation Unit). Randomisation will be stratified by pre-operative function measured by the Lower Extremity Functional Scale [27] (categorised as high or low function based on mean scores from a published study with a similar patient cohort [28]) and recruitment centre (Southmead Hospital or Emersons Green Treatment Centre). Blinding of participants and trial personnel to treatment allocation will not be possible due to the nature of the intervention.

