### Statistical analysis

Analysis will follow a Statistical and Health Economics Analysis Plan which will have been approved a priori by the Trial Steering Committee. Data presentation and analysis will be in accordance with Consolidated Standards of Reporting Trials (CONSORT) guidelines. Baseline characteristics will be reported by trial arm using percentages, means (SDs) or medians (interquartile ranges) as appropriate. The repeated measures of primary and secondary outcomes will be plotted by trial arm.

The main analysis will consist of a linear mixed regression (with random intercept for patient to control for the repeated follow-ups) with an interaction between the intervention effect and the assessment time adjusted for pre-operative function and recruitment centre. The use of these interactions terms will allow us to assess and single out the specific effect of the intervention on LEFS at 12 months post-operative, and then identify the intervention-specific effects at 3 and 6 months post-operative (secondary outcomes). The regression will then be adjusted for imbalanced individual characteristics between arms at baseline. Other types of generalised linear mixed models will be considered if the former approach is not fitting the distribution of the residuals of the regressed (transformed) primary or secondary outcomes. The model will finally be adjusted for type of additional physiotherapy treatment received (physiotherapy received that is not delivered as part of the intervention). The trial is not powered for such adjustments and it will only inform us on their potential impact on the intervention effect.

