The analyses will be conducted on an intention-to-treat basis with and without imputation of missing primary outcome data. A multiple imputation (MI) by chained equations under a missing at random framework stratified by randomization arm will be used [47]. These imputed results will be contrasted with other imputation strategies as discussed by White and colleagues [48]. The same modelling strategy will be used to investigate the intervention effect on the KOOS, HADS and patient satisfaction. A sensitivity analysis will investigate the intervention effect using a per-protocol analysis. Information clustering at the recruitment centre level will be addressed using a fixed-effect indicator and clustering of outcomes by surgeon will be investigated and modelled if required. We will also compare the mean/median primary outcome by physiotherapist for patients receiving the intervention and any significant differences will be used to conduct exploratory sub-group analyses. Given the differences in outcomes after TKR for men and women [49], exploratory analysis will be undertaken to investigate the impact of gender.

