### Health economic analysis

The primary economic evaluation will follow NICE guidelines [50] and will be a cost-utility analysis (CUA), comparing the incremental costs with incremental QALYs gained, from an NHS and Personal Social Services (PSS) perspective, at 12 months post-operative. Secondary analyses will include taking a societal perspective on costs, and a cost-effectiveness analysis comparing the incremental costs with the primary clinical outcome at 12 months. All analyses will follow a Statistical and Health Economics Analysis Plan.

Resources will be valued using unit cost estimates from national tariffs [51, 52], and liaising with hospital finance departments if necessary. We will assign UK preference-based utility weights [53] to patients’ answers to the EQ-5D-5L questionnaire, and produce unadjusted 1-year QALY scores per arm, using the area under the curve approach [54]. Costs and QALY estimates will then be adjusted for stratification variables, and also for baseline utility [55] for QALYs, using regression methods. Costs and outcomes will be compared between arms to determine dominance, i.e. whether one arm is more effective and costs less than the other. Missing data will be imputed using multiple chained equations [47].

The economic result will be bootstrapped incremental net monetary benefit (INMB) statistics, using a range of societal willingness-to-pay thresholds for a QALY gained. If no arm is dominant, we will compute incremental cost-effectiveness ratios (ICERs) in relation to both outcomes. The primary results will report estimates based on complete datasets with imputed data. We will plot adjusted bootstrapped costs and effects in cost-effectiveness planes and create cost-effectiveness acceptability curves to consider uncertainty around the adoption decision. In sensitivity analysis we will explore sources of methodological and parameter uncertainty, such as costing assumptions.

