## Discussion

This project is a fully powered RCT to evaluate the long-term clinical effectiveness and cost-effectiveness of a novel group-based outpatient physiotherapy intervention following TKR in addition to usual care. The trial includes patients with all levels of functional aspirations, and emphasises the concept of participation in valued activities as a basis for effective and appropriate rehabilitation goals. Our approach aims to both improve function for those patients who may otherwise have unfavourable outcomes, and assist patients who are recovering well to achieve more demanding goals.

A strength of this trial is that the design of the intervention and trial were informed by prior feasibility work [25]. In particular, the feasibility work highlighted the importance of complementing the collection of outcome measures by postal questionnaire with telephone calls to maximise completion rates. This has previously been shown to be an effective strategy with a similar patient population [56], although with the increasing uptake of technology, online questionnaires may be a useful alternative data collection method for future trials. Another strength of this trial is the 12-month follow-up period, which will allow assessment of the long-term impact of physiotherapy on patient outcomes and resource use. However, in addition to patient-reported outcome measures, the trial may have benefitted from the inclusion of more objective measures of function, such as muscle strength or gait analysis, as these capture different dimensions of function [57]. Another limitation of the trial which warrants acknowledgement is the lack of blinding, because of the group-based nature of the physiotherapy intervention. Blinding in trials of physiotherapy is often challenging and only a quarter of physiotherapy trials are blinded [58]. There is a risk that lack of blinding will introduce bias as outcome data will be self-reported by participants who will know which treatment they have been allocated to. A recent meta-epidemiology study found that lack of blinding in physiotherapy trials can lead to an underestimation of the treatment effects compared to trials with blinding, although this was not statistically significant [58]. In addition, while the trial is powered for our primary analysis, other analyses are purely exploratory in nature and will be interpreted as such.

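### The statement that trial personnel cannot be blinded is wider than its reason: the trial statistician could fit and lock the primary LEFS model on neutrally coded arms

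*Protocol article*

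**What the plan says.** The Randomisation section of the protocol article makes one statement on blinding: "Blinding of participants and trial personnel to treatment allocation will not be possible due to the nature of the intervention". It does not define trial personnel and makes no exception. The Discussion lists as a limitation "the lack of blinding, because of the group-based nature of the physiotherapy intervention". The only resulting bias it describes is that "outcome data will be self-reported by participants who will know which treatment they have been allocated to".

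The Statistical analysis section fixes the main model for the LEFS: a linear mixed regression with a random patient intercept and an arm-by-time interaction, adjusted for baseline function and centre. It then leaves some steps to be settled on the data:

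- on model form: "Other types of generalised linear mixed models will be considered if the former approach is not fitting the distribution of the residuals";
- on surgeons: "clustering of outcomes by surgeon will be investigated and modelled if required";
- on covariates: "The regression will then be adjusted for imbalanced individual characteristics between arms at baseline".

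The same section gives a safeguard: "Analysis will follow a Statistical and Health Economics Analysis Plan which will have been approved a priori by the Trial Steering Committee". That plan is not available here.

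**The concern.** The sentence gives one reason and applies it to everyone working on the trial. The reason is sound for people who attend, run or hear about the classes. It is not a reason for the person who fits the primary model, who need not meet participants and can work from a file in which the arms carry neutral labels.

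The primary outcome is reported by participants who know their allocation, so masking is already lost at treatment and at outcome collection. Primary analysis is one of the few stages where it is still available. If the statistician knows which arm is which while deciding whether the residuals are acceptable or whether a surgeon term is needed, knowledge of which choice favours the classes could affect the main result, or be suspected of doing so. The Discussion does not consider this source of bias.

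**Working it through.** No arithmetic applies. The sample size rests on a 9-point difference, an SD of 18.4, the 1.12² inflation, 35% missing data, 80% power and a two-sided 5% level. None of these depends on who is blinded, so the total of 256 is unaffected. The check is to ask, for each role and each analysis step, whether the stated reason applies.

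**Roles**

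- Participants: they know whether they attend classes. The reason applies.
- Physiotherapists and assistants: they deliver the classes. The reason applies.
- Researchers who telephone participants: the section on patient satisfaction and adherence has them ask class attenders about the classes. The reason applies.
- Trial statistician fitting the LEFS model: the inputs are LEFS scores, time, centre, baseline function, surgeon and an arm label. Nothing in the group format prevents that label from being A or B. The reason does not apply.
- Health economist: the Resource use section has class-delivery resources recorded by the physiotherapists, so these costs arise in one arm only. The reason applies in large part.

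**Steps in the Statistical analysis section**

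- Residual fit and transformation: uses outcome data. The check is the same whichever arm is called A. Coded arms suffice.
- Surgeon clustering: uses outcome data and surgeon identity. Coded arms suffice.
- Adjustment for baseline imbalance: compares the arms on baseline data, not outcomes. It needs two labels but not their meaning. Coded arms suffice.
- Multiple imputation stratified by arm: needs two groups but not their meaning. Coded arms suffice.
- Comparison of physiotherapists: confined to participants who received the classes. The arm must be known.
- Per-protocol analysis: depends on what was attended. The arm must be known.
- Adjustment for physiotherapy received outside the trial classes: such physiotherapy has to be told apart from the classes, so this step belongs after unmasking.
- All cost analyses: the arm is revealed by delivery costs.

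The steps that shape the primary LEFS result can therefore be carried out on coded arms. The steps that cannot are sensitivity, exploratory or economic analyses, and they can follow release of the codes.

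**The case against.** The strongest objection is that the article never mentions the statistician. The sentence closes a paragraph on allocation, and trial personnel may mean only those who deliver care and collect data. Arrangements for coded datasets commonly sit in the analysis plan, which was to be approved in advance and is not shown. This stands in part. A reader might infer that the analysts will make modelling decisions knowing the arms, but the article does not say so; that is only the literal reading of an undefined term. Had the article been silent on masking of personnel, there would be no point to raise. It is not silent: it says such blinding is impossible, without exception, and a plan that masked the statistician would conflict with that sentence as written.

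Three further readings are tempting and should not be adopted.

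- **That the health economist should be masked too.** Delivery costs exist in one arm only, so this is not realistic.
- **That costing choices could steer the main result.** The plan to "explore sources of methodological and parameter uncertainty, such as costing assumptions" belongs to sensitivity analysis, so it does not touch the primary result.
- **That an inflated type I error can be attached to this point.** Any such figure would measure free choice among models. An analyst who sees only A and B can still pick the smallest p-value, so coded labels do not remove that inflation. They remove only the ability to steer towards a known arm. The plan also ties model changes to residual fit and to need, not to free choice.

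Masking would also be imperfect. In the feasibility study, missing LEFS scores at 6 months were 9% in the intervention group and 35% in usual care. A similar gap in the trial would hint at which code is which.

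**Conclusion.** The point holds in a narrow form. The blanket statement is wider than its reason, and for the primary LEFS model and its checks the reason fails. Coded arms are feasible there and would change how the analysis is conducted.

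The size of the benefit cannot be derived from the document. It is protection against analyst bias, probably small, because the main model is already specified and an analysis plan is to be approved beforehand. The conclusion assumes that trial personnel is read literally and that the residual and surgeon decisions are still made on observed outcome data. If the approved plan already fixes those decisions or already masks the statistician, only the wording in the Randomisation section and the Discussion needs to be brought into line.

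**What to change.** Replace the blinding sentence in the Randomisation section with text such as:

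> Participants, staff delivering the classes and researchers in contact with participants cannot be blinded. The trial statistician will work with neutral arm codes, with class attendance and class-feedback variables withheld, until the LEFS model form, surgeon term and imputation model are locked and dated under the approved analysis plan; codes are then released.

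State that the per-protocol, physiotherapist, additional-physiotherapy and all cost analyses follow release of the codes, and narrow the limitation in the Discussion to the same named roles.

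The cost is the preparation of a coded dataset, a dated lock note and a short delay to the analyses that need the arm. No further data are required. The Study duration section expects 12-month follow-up to finish by December 2017, so the change can be made before the primary data are complete.
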